### Inclusion and exclusion criteria

The inclusion criteria of this trial are (1) chronic primary musculoskeletal pain is clinically diagnosed based on the criteria that chronic primary musculoskeletal pain is chronic pain in the muscles, bones, joints or tendons that is characterized by significant emotional distress such as anxiety, anger/frustration or depressed mood or functional disability such as interference in daily life activities and reduced participation in social roles, including fibromyalgia syndrome which is defined as diffuse pain in at least 4 of 5 body regions which is associated with significant emotional distress or functional disability; (2) chronic musculoskeletal pain symptoms more than 3 months; (3) pain severity of Numerical Rating Scale (NRS) pain score between 4 and 6; (4) pain is often related to weather changes, and symptoms can be aggravated after rainy days and fatigue; (5) age between 18 years and 80 years; (6) volunteer to participate in the trial and sign the informed consent.

The exclusion criteria of this trial are (1) acute pain or chronic secondary musculoskeletal pain or chronic cancer related pain or chronic neuropathic pain; (2) history of cardiovascular and cerebrovascular diseases, liver diseases, kidney diseases, blood system diseases, diabetes, or infectious diseases; (3) history of tuberculosis, rheumatoid arthritis, ankylosing spondylitis, gout, or cancer bone metastasis; (4) history of mental disorders or communication dysfunction; (5) history of peripheral nerve perception disorder; (6) pregnant, lactating women or those who have pregnancy plans; (7) surgical plan in the next 3 months; (8) reported allergy to the interventions in this trial; (9) have used pain killers or received other pain treatment within the last 1 week.

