### Baseline assessment

Baseline visit and assessment will be conducted at the inpatient centers in the hospitals. Demographic information (including sex, age, educational background, job), course of the chronic pain, medical history (including complications, smoking, alcohol), and basic tests (including blood pressure, heart rate), will be collected in person. Baseline assessment about the chronic musculoskeletal pain will include severity of the pain (assessed by Numerical Rating Scale, range 0–10, higher scores indicate worse pain), pain-related overall life assessment (measured by Global Pain Scale, range 0–200, higher scores indicate worse influence on life), acceptance of pain (assessed by Chronic Pain Acceptance Questionnaire, range 0–120, higher scores indicate higher pain acceptance), health education and self-management (assessed by the Health Education Impact Questionnaire, range 40–200, higher scores indicate better health self-management), pain-related self-efficacy (assessed by the Pain Self-Efficacy Questionnaire, range 0–60, higher scores indicate better confidence of self-efficacy), anxiety and depression (assessed by the Hospital Anxiety and Depression Scale, range 0–42, higher scores indicate more severe symptoms), and quality of life (assessed by Short Form-36, range 0–100, higher scores indicate better health). All scheduled visits are shown in the Table 1.

**Table 1 tab1:** The schedule of planned visits.

Study component	Visit 1	Visit 2	Visit 3	Visit 4	Visit 5	Visit 6	Visit 7	Visit 8
Time	1 d before treatment	First treatment	7 ± 1 d after treatment	14 ± 1 d after treatment	21 ± 1 d after treatment	28 ± 1 d after treatment	35 ± 1 d after treatment	42 ± 1 d after treatment
Informed consent	×	–	–	–	–	–	–	–
Demographic	×	–	–	–	–	–	–	–
Pain duration	×	–	–	–	–	–	–	–
Pain locations	×	–	–	–	–	–	–	–
Pain triggers	×	–	–	–	–	–	–	–
Randomization	×	–	–	–	–	–	–	–
Intervention	–	×	×	×	–	–	–	–
NRS	×	–	×	×	–	–	–	×
GPS	×	–	×	×	–	–	–	×
CPAQ	×	–	×	×	–	–	–	×
heiQ	×	–	×	×	–	–	–	×
PSEQ	×	–	×	×	–	–	–	×
HADS	×	–	×	×	–	–	–	×
SF-36	×	–	×	×	–	–	–	×
Pain killer intake	×	–	×	×	–	–	–	×
Adverse events	–	×	×	×	×	×	×	×

NRS, Numerical rating scale; GPS, Global pain scale; CPAQ, Chronic pain acceptance questionnaire; heiQ, Health Education Impact Questionnaire; PSEQ, Pain Self-Efficacy Questionnaire; HADS, Hospital anxiety and depression scale; SF-36, Short Form-36.

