### Power analysis and sample size calculation

The power analysis and sample size estimation were based on the primary outcome of this trial which is the change in GPS from baseline to the end of the 2 week intervention. One of our pilot studies showed that the mean change in GPS in heat-stone group was 12, while the mean change in GPS in flurbiprofen was 8, with a combined standard deviation of 6.7. With a power of 80%, 2-sided alpha of 0.05, and the assumption that the change is normally distributed, we used the “power twomeans” function in STATA with 1:1 ratio in treatment and control group to get estimated sample size of 46 samples for each group, so that a total of 92 participants are required. Considering the 20% dropout rate, the total sample size of 115 is required. To make it convenient to assign the participants with 2:1:1 ratio to the 3 centers, we took the 120 as the final planned sample size. The sample size was calculated using STATA, version 16.1 (StataCorp, USA).

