### Statistical analysis

The Primary analysis will be conducted on the full dataset of all the participants after randomization based on the intention-to-treat principle. Moreover, sensitivity analysis will be conducted between the full dataset and the per protocol dataset. Participants who are not in the per protocol analysis are nonadherence which might be caused by failure to receive the assigned treatment, suffering from severe adverse events, or loss of follow-up.

To check if there is selection bias and confounding factors, we will compare the baseline characteristics of the two groups. Continuous variables will be described as mean (Standard Deviation) for normal distribution and be tested using t test or be described as median (interquartile range) for skewed distribution and be tested using Mann–Whitney test. Categorical variables will be summarized as counts (percentages) and be tested using Chi squared test or Fisher exact test.

The primary outcome of this trial is the change in Global Pain Scale from baseline to the end of the 2 week intervention. The difference of the changes between the two groups will be analyzed using a generalized linear mixed model. The mean and 95% confidence interval will be calculated and estimated. Known confounding factors that may affect the pain severity in chronic musculoskeletal patients include age, sex, job, duration of the chronic pain, and emotional state. Therefore, we will make the subgroup analysis for the variables of age categories (>60 years vs. ≤60 years), sex (female vs. male), job categories, duration of pain, taking these as covariates in the model.

For the secondary outcomes, generalized linear mixed model will be used for continuous variables, and two proportion z test will be used for proportions, whereas the Chi squared test or Fisher exact test will be used for categorical variables.

The primary economic analysis will be the cost-utility analysis over 6 week using quality-adjusted life years (QALYs) calculated from the SF-36. The mixed-effect linear regression model will be used, adjusting the confounding factors including age, sex, job, and site of recruitment.

All statistical tests will use the statistical significance of 2-sided *p* value of <0.05. All the statistical analysis will be performed using Python, version 3.8.16 (sklearn and statsmodels packages).

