## Discussion

This is the first randomized clinical trial to investigate the heat-stone massage as a kind of therapy alone to treat chronic musculoskeletal pain. Currently, no massage therapy has been recommended by any of the chronic musculoskeletal pain management guideline due to lack of evidence. Finding a therapy which is easy to use and has long-term effect with low cost for the management of chronic musculoskeletal pain will change the clinical practice of this chronic pain and will change the life quality of the patients. Our pilot study showed a promising result in terms of long-term symptoms relief, but we need strong evidence to prove this. The results of this multicenter, randomized, clinical trial will provide high-quality evidence, which is promising to change the guideline for chronic pain management in the future.

The strengths of this study include: (1) randomization can reduce the selection bias and control both measured and unmeasured confounding factors; (2) inclusion criteria of chronic musculoskeletal pain and standard procedure of the heat-stone massage increase the external validity and application of the intervention; (3) prespecified subgroup analysis can identify any interaction on the causal pathway between the heat-stone massage and pain relief outcome, which will effect modifiers that are crucial when we interpret the results.

This trial also has limitations. First, this trial is only blinded to principal investigator, outcome assessment staff, and outcome analysis statistician, but not blinded to participants or massage therapists, therefore there might be performance bias. Nevertheless, we design the expectation score to evaluate if the expectation is different between groups after they know what we are receiving. Second, although the trial has follow-up visits of 1-month, longer term effect cannot be known, which somehow limits the interpretation of long-term effect of pain relief. Third, we only recruit patients with the moderate pain assessed by NRS score in the range of 4–6, based on the results of our pilot study showing that patient with NRS score between 4 and 6 benefited from the heat-stone massage. This will restrict the chronic pain population that the results of this study can be generalized to, and patients with more severe pain may not benefit.

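### Age enters the analysis only as over 60 versus 60 or under; using age in years is a cheap, low-priority gain for the treatment-by-age analysis and barely affects the primary comparison

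*Protocol article*

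**What the plan says.** The Statistical analysis section first lists the factors thought to matter: "Known confounding factors that may affect the pain severity in chronic musculoskeletal patients include age, sex, job, duration of the chronic pain, and emotional state". It then plans subgroup analyses by several variables. Age is given as "age categories (>60 years vs. ≤60 years", and the sentence ends with "taking these as covariates in the model". Read plainly, the two-level age variable does two jobs: it defines the subgroup and it adjusts the model.

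Under Inclusion and exclusion criteria the eligible range is "age between 18 years and 80 years". Under Baseline assessment, age is an ordinary demographic item with no categories attached: "Demographic information (including sex, age, educational background, job". The recording format is not stated. No reason is given for cutting at 60, and no analysis of effect modification on continuous age is mentioned. The economic model in the same section adjusts for age without categories.

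The Discussion counts the subgroup work as a strength: "prespecified subgroup analysis can identify any interaction on the causal pathway between the heat-stone massage and pain relief outcome".

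**The concern.** A split at 60 treats a patient of 61 like one of 80, and a patient of 60 like one of 18. If response to treatment changes gradually with age, most of that gradient is hidden inside the two groups. The trial is sized only for the main effect, so little information is available for interactions, yet the Discussion expects effect modifiers to be found. What is at stake is the age subgroup result and, to a much smaller degree, the precision gained by adjusting for age.

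**Working it through.** **1. The plan's own sample size.** Power analysis and sample size calculation states that "the mean change in GPS in heat-stone group was 12, while the mean change in GPS in flurbiprofen was 8", with a combined SD of 6.7, 80% power and two-sided alpha 0.05.
- Difference: 12 − 8 = 4.
- Normal approximation: n = 2 × (1.960 + 0.842)² × 6.7² / 4² ≈ 44.04, so 45 per group. The t-based solution is 45.02, so 46.
- Total 92, and 92 / 0.80 = 115, rounded in the plan to 120. The stated figures reproduce.
- Evaluable patients out of 120 at 20% dropout: 120 × 0.80 = 96. No power is stated for the age subgroup.

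**2. Information kept by the split.** For a linear trend this is the squared correlation between age and the over-60 indicator. For a normal age distribution it is φ(z)² / [p(1 − p)], with z = (60 − mean)/SD and p the share over 60. For a uniform distribution it is 3p(1 − p). All age distributions below are assumptions.

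| Assumed age | p over 60 | Kept | Lost |
|---|---|---|---|
| Mean 45, SD 14 | 0.142 | 0.2247² / 0.1218 = 0.41 | 59% |
| Mean 50, SD 14 | 0.238 | 0.3091² / 0.1811 = 0.53 | 47% |
| Mean 55, SD 12 | 0.339 | 0.3658² / 0.2239 = 0.60 | 40% |
| Mean 60, SD 12 | 0.500 | 0.3989² / 0.25 = 0.64 | 36% |
| Uniform 18–80 | 20/62 = 0.323 | 3 × 0.323 × 0.677 = 0.66 | 34% |

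Limiting the normal cases to 18–80 moves the share kept by at most about 0.02. Younger and narrower samples lose more: 73% at mean 45, SD 10.

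**3. Power of the treatment-by-age test.** Assume an interaction term is fitted, N = 96, residual SD 6.7, and age with mean 52 and SD 14 limited to 18–80. Its actual SD is then about 12.8, and the split keeps about 0.56. For an effect changing by θ points per 14 years:
- Continuous age: Φ(θ × (12.8/14) × √96 / (2 × 6.7) − 1.96).
- Split age: the same, with the first term multiplied by √0.56.
- Example, θ = 4: the first term is 2.67, so power is Φ(0.71) ≈ 76%. With the split it is about 2.00, so about 51%.

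| θ per SD of age | Formula: years vs split | Simulation: years vs split |
|---|---|---|
| 4 | 76% vs 51% | 75% vs 49% |
| 3 | 52% vs 32% | 51% vs 30% |
| 2 | 27% vs 17% | 26% vs 16% |

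A further run of 3,000 trials per setting gave 72% vs 45%, 50% vs 30% and 25% vs 16%. Type I error was about 5% for both codings.

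**4. Cost to the primary comparison.** If continuous age explains a share R² of outcome variance and the split keeps a fraction k of that, the standard error is multiplied by √[(1 − kR²)/(1 − R²)].
- R² = 5% (assumed): 1.009 at k = 0.66, 1.015 at k = 0.41.
- R² = 10% (assumed): 1.019 at k = 0.66, 1.032 at k = 0.41.

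**5. If the effect steps at 60.** With N = 120, uniform age and a true step of 7.3 points, simulated power is 78% with the split and 59% with continuous age.

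**The case against.** A subgroup cut fixed in advance is conventional and easy to report, and it prevents a search for a cut-point in age. Linearity is an assumption too, and step 5 shows that the split wins if the effect jumps at 60. Both points stand, although the article argues for no such jump.

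The larger interactions above are also hard to believe. With a main effect of 4, a change of 4 points per SD takes the effect from 4 − 8 = −4 at two SDs below the mean age to 4 + 8 = 12 at two SDs above. At the more moderate 2 points per SD both codings mostly fail. Sample size is the main limit there, and recoding age does not change it. This stands, and it is why the point has low priority.

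The covariate sentence can also be read as applying the categories to the subgroup analysis alone. The plain mention of age in the list of factors and in the economic model gives that reading some support, so dual use is the natural reading and not a certain one.

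A reader might go further in three ways that the documents do not support:
- **That the split loses most of the power.** It does not: about 60% to 65% of the power remains in each setting shown (49/75, 30/51, 16/26).
- **That the primary result is biased.** Arms are randomised, so the coding of a baseline covariate does not bias the treatment estimate. The precision cost is the small one in step 4.
- **That pain duration will be cut after the data are seen, inflating false positives.** The article lists duration without any cut and describes no cut-point search. Detail on its coding is something an article may leave to the full protocol or analysis plan.

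**Conclusion.** The point holds as a modest one. The article commits to a two-level age variable where age in years should be available. Under a roughly linear trend and the assumed age distributions, that gives up about 34% to 59% of the information in age. It lowers interaction power by about 10 percentage points for a moderate interaction and by about 20 to 26 for very large ones. The test is weak for moderate interactions with either coding, so the Discussion's expectation of finding effect modifiers is optimistic regardless. The primary comparison is essentially untouched: no bias, and about 1% to 3% on the standard error if age explains 5% to 10% of variance. That age is recorded in years is inferred from the baseline list and the eligibility range. This is an inexpensive improvement to a secondary analysis and does not threaten the trial's main conclusion.

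**What to change.** In the Statistical analysis section, state that age enters the model in years as a covariate. State also that effect modification by age is tested with a treatment-by-continuous-age term, with one added curvature term to check linearity. Keep over 60 versus 60 or under as a descriptive display of the estimated effect in each group.

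The change is wording only, with no new data, visits or patients. Its cost is reliance on a roughly linear trend: if the effect truly changed abruptly at 60, the split would have been the stronger test. The curvature check and the retained display limit that risk without removing it.

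### The subgroup analysis is specified only as covariates in the model, which does not support the Discussion's claim that it can identify any interaction

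*Protocol article*

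**What the plan says.** The primary-outcome paragraph of the Statistical analysis section runs in four steps.

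- Model: "The difference of the changes between the two groups will be analyzed using a generalized linear mixed model".
- Reason: "Known confounding factors that may affect the pain severity in chronic musculoskeletal patients include age, sex, job, duration of the chronic pain, and emotional state".
- Analysis drawn from that reason: "Therefore, we will make the subgroup analysis for the variables of age categories" (over 60 against 60 or younger), followed by sex, job and pain duration.
- Method: "job categories, duration of pain, taking these as covariates in the model".

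The section mentions no treatment-by-factor term, no interaction test and no subgroup-specific treatment effects.

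The Discussion, listing the study's strengths, says that "prespecified subgroup analysis can identify any interaction on the causal pathway between the heat-stone massage and pain relief outcome", and goes on to speak of effect modifiers.

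**The concern.** Two tasks are treated as one. Covariate adjustment deals with factors that predict the outcome and yields a single treatment effect averaged over them. Subgroup analysis asks whether the treatment effect differs between levels of a factor. The article justifies the second task by confounding, describes it with the tool for the first, and then claims the result that only an interaction term can give.

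What is at stake is the reading of subgroup results. If the analysis is run as written, a coefficient for age or sex could be taken as evidence of who benefits from heat-stone massage, when it reflects how patients of that age or sex fare on average over both arms. The article hopes to influence guidelines, so a statement about who benefits would carry weight.

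**Working it through.** **1. The plan's own sample size.** Inputs, from Power analysis and sample size calculation: "the mean change in GPS in heat-stone group was 12, while the mean change in GPS in flurbiprofen was 8", a difference of 12 − 8 = 4 points; "with a combined standard deviation of 6.7"; "With a power of 80%, 2-sided alpha of 0.05"; 1:1 allocation; 20% dropout. The two-sample t calculation gives 45.02 per arm, rounded up to 46, so 92 in total. Then 92 / (1 − 0.20) = 115, and 120 is planned. These figures reproduce. The article gives none for subgroups or interactions.

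**2. What a covariate-only model estimates.** Take a two-level factor, balanced across arms. Let the two levels differ by c in the control arm and by c + i in the heat-stone arm, where i is the interaction. A model with treatment and factor as main effects returns:

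- one treatment effect, averaged over the two levels;
- one factor coefficient equal to the mean of the two differences, c + i/2.

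Since c is unknown, the same coefficient fits any value of i. The model carries no separate information on i.

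**3. Check by simulation.** 1,000 runs, N = 92, SD 6.7, two equal subgroups with true treatment effects of 8 and 0 points (mean 4). The two subgroups were given the same average outcome over both arms, that is c = −i/2.

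| Model | Result with true effects 8 and 0 |
|---|---|
| Treatment + factor | one common effect of about 3.9; factor coefficient significant in 4.8% of runs |
| Treatment × factor | interaction of about 8.0 in size; significant in 81% of runs |

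With no true interaction, the rejection rates were 4.1% (factor coefficient) and 4.7% (interaction), both near the nominal 5%. A large difference in effect thus left no trace in the covariate-only model.

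**4. Power if the right term is used (context).** With N evaluable patients and a share s in one subgroup:

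SE(interaction) = SD × √[4/(N·s) + 4/(N·(1 − s))]

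For N = 92 and s = 0.5: 6.7 × √(4/46 + 4/46) = 2.79. For a 4-point interaction, 4/2.79 = 1.43, and power is Φ(1.43 − 1.96), about 30%. The article gives no subgroup shares, so s is an assumption. N runs from the 92 required, through 120 × 0.8 = 96, to all 120.

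| Evaluable N | s = 0.5 | s = 0.3 | s = 0.2 |
|---|---|---|---|
| 92 | 30% (SE 2.79) | 26% (SE 3.05) | 21% (SE 3.49) |
| 96 | 31% (SE 2.74) | 27% (SE 2.98) | 22% (SE 3.42) |
| 120 | 37% (SE 2.45) | 32% (SE 2.67) | 26% (SE 3.06) |

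For 80% power at s = 0.5, N = (1.96 + 0.84)² × 6.7² × 4 × (1/0.5 + 1/0.5) / 4², which is 353 evaluable patients with unrounded normal quantiles. That is about 3.8 times the 92 required for the main comparison.

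**The case against.** The strongest reply is that the article gives no model equation. It says subgroup analysis, gives categories for age and sex, and in the Discussion describes the aim as interaction. For the economic model it speaks plainly of adjusting, a different word. So the covariate phrase may be loose English for putting the factors into the model to examine effect modification, and a SAP that is not shown may supply the term. This has force, and it rules out saying that the investigators have decided against interaction terms. It does not remove the point: the article names a method and ties it to confounding, and that method does not match the purpose stated in the Discussion.

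Three stronger readings are tempting, and the article does not support them.

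- A reader might infer that the trial's main result is compromised. No subgroup result is among the primary or secondary outcomes, the sample size does not depend on one, and randomisation protects the comparison of GPS change with or without these covariates.
- A reader might infer that age is dichotomised at 60 for adjustment, with loss of information. The cut is given for the subgroup analysis; the economic model lists age without a cut.
- A reader might take the low power as the size of the error. It is not. Low interaction power is normal in a trial sized on its main effect and would remain with a correctly specified term. It bears only on the promise to find any interaction. The figures also apply to two-level factors, so not directly to job, which may have more levels, or to pain duration, for which the article states no cut.

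**Conclusion.** The point holds as a mismatch between stated method and stated purpose. As written, the subgroup analysis is covariate adjustment, and covariate adjustment cannot estimate or test effect modification. The Discussion's claim is therefore unsupported by the method, and its reach would still be too wide with the right term: power is about 21% to 37% for a two-level interaction of 4 points. That range rests on the article's SD of 6.7, a two-sided 5% level, 92 to 120 evaluable patients and assumed subgroup shares of 20% to 50%. The conclusion about the method rests on none of these assumptions. Severity: should be fixed. The consequence is confined to subgroup inference and its wording.

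**What to change.** - **Separate the two tasks.** State in its own sentence whether the primary model is adjusted for covariates and for which ones. The subgroup repair does not require any particular covariate set.
- **Specify the subgroup analysis.** For each of age category, sex, job and pain duration, fit a model with treatment, the factor and a treatment-by-factor term. Report the treatment effect in each subgroup with its 95% confidence interval, and the interaction p-value. Label all of these exploratory. Do not infer differential benefit from covariate coefficients or from separate p-values within subgroups.
- **Replace the Discussion sentence**, for example with: *Exploratory subgroup analyses will examine whether the treatment effect varies by age, sex, job and pain duration; the trial was sized for the main comparison, and power to detect interaction is low.*

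The cost is a few lines in the Statistical analysis section, one Discussion sentence and one extra model per factor. The four factors are already collected at baseline, and the sample size and primary comparison do not change.

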**Methods and analysis:**

This multicenter, 2-arm, randomized, positive drug-controlled trial will include a total of 120 patients with chronic musculoskeletal pain. The intervention group will receive a 2 week heat-stone massage, 3 times per week, whereas the control group will receive the flurbiprofen plaster twice per day for 2 weeks. The primary end point is the change in Global Pain Scale from baseline to the end of the 2 week intervention. The secondary outcomes include the pain severity (Numerical Rating Scale), pain acceptance (Chronic Pain Acceptance Questionnaire), self-management (Health Education Impact Questionnaire), self-efficacy (Pain Self-Efficacy Questionnaire), anxiety and depression (Hospital Anxiety and Depression Scale), quality of life (Short Form-36). The intention-to-treat dataset will be used for analysis.

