### Study outcomes and assessment

The primary outcome is the change in the score of Global Pain Scale (GPS, range 0–200, higher scores indicate worse influence on life) from baseline to the end of the 2 week intervention. The GPS is a validated, concise, and easily interpreted score to comprehensively assess the pain, emotions, clinical outcomes, and daily activities (11). The Chinese version of the GPS was also validated in Chinese population (12).

The secondary outcomes include (1) the change in GPS from baseline to the end of 6 week follow-up; (2) the proportion of participants who have clinically significant change in severity of the pain assessed by Numerical Rating Scale (NRS, range 0–10, higher scores indicate worse pain) (13), a change of 20% from baseline to the end of the 2 week intervention is regarded as clinically significant change (14); (3) the change in acceptance of pain assessed by Chronic Pain Acceptance Questionnaire(CPAQ, range 0–120, higher scores indicate higher pain acceptance) from baseline to the end of 2 week intervention (15); (4) the change in health education and self-management assessed by the Health Education Impact Questionnaire (heiQ, range 40–200, higher scores indicate better health self-management) from baseline to the end of 2 week intervention (16); (5) the change in pain-related self-efficacy assessed by the Pain Self-Efficacy Questionnaire (PSEQ, range 0–60, higher scores indicate better confidence of self-efficacy) from baseline to the end of 2 week intervention (17); (6) the change of anxiety and depression assessed by the Hospital Anxiety and Depression Scale (HADS, range 0–42, higher scores indicate more severe symptoms) from baseline to the end of 2 week intervention (18); (7) the change in quality of life assessed by Short Form-36 (SF-36, range 0–100, higher scores indicate better health) from baseline to the end of the 2 week intervention (19).

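### The week-2 NRS responder outcome is given an unadjusted two-proportion z test, which on observed scores compares completers only and ignores baseline NRS, day-7 NRS and centre

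*Protocol article*

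**What the plan says.** Study outcomes and assessment defines the second secondary outcome as a responder proportion on the NRS: "a change of 20% from baseline to the end of the 2 week intervention is regarded as clinically significant change". Each patient is therefore a yes or a no, and the answer needs a week-2 score.

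Statistical analysis separates the methods by type of variable. "For the secondary outcomes, generalized linear mixed model will be used for continuous variables", and for the responder outcome a "two proportion z test will be used for proportions". No covariates are named for the latter.

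On the analysis set, the abstract says "The intention-to-treat dataset will be used for analysis" without limiting it to one outcome. The Statistical analysis section is narrower: "The Primary analysis will be conducted on the full dataset of all the participants after randomization based on the intention-to-treat principle". That section also gives the reasons for being outside the per-protocol set, "failure to receive the assigned treatment, suffering from severe adverse events, or loss of follow-up", so patients lost to follow-up are meant to stay in the full set.

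Power analysis and sample size calculation allows for losses: "Considering the 20% dropout rate, the total sample size of 115 is required". Table 1 schedules the NRS at baseline, day 7, day 14 and day 42. Randomization and blinding says that a separate list is produced for each of the three centres.

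**The concern.** A z test takes one yes or no per patient. Applied to the scores that exist, it removes patients without a week-2 NRS from numerator and denominator alike. The result is a completers' proportion, although the abstract promises an intention-to-treat dataset.

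The trial is open to patients and therapists, and the safety section expects burns, bruising and heavy sweating with the heat-stone treatment. Reasons for leaving could therefore differ by arm, and a completers' comparison could then be biased.

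The named test also discards information the trial will hold. Baseline NRS is recorded before treatment, day-7 NRS exists for anyone who leaves after that visit, and centre is a randomization stratum. The continuous outcomes get a mixed model, which can use partial follow-up if fitted to the repeated scores. The responder outcome gets nothing comparable.

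**Working it through.** **1. The plan's own figure.** Inputs from the sample-size section: mean GPS changes 12 and 8 (difference 4), SD 6.7, power 80%, two-sided alpha 0.05. The normal approximation gives 2 × (1.96 + 0.84)² × (6.7/4)² ≈ 44, or 45 per arm at full precision after rounding up. The t-based calculation gives 45.02, rounded up to 46. Then 2 × 46 = 92 and 92/0.80 = 115. The stated figures reproduce. No power is stated for the responder outcome.

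**2. Patients affected if the allowance were used up.** 0.20 × 120 = 24 without a score, leaving 96, or 48 per arm. Since 96 exceeds 92, the primary outcome keeps its planned number.

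**3. Precision.** Response rates are not given; assume 60%. The standard error of the difference is √(2 × 0.6 × 0.4/60) = 0.089 with 60 per arm and √(2 × 0.6 × 0.4/48) = 0.100 with 48. The ratio is √(60/48) = 1.118, so the standard error is 11.8% larger. Most of this comes from the missing data, not from the choice of test.

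**4. Bias by formula.** If the true response is P, a fraction d leaves and leavers respond at rate r, completers show (P − d × r)/(1 − d). Take P = 0.60 and d = 0.20 in both arms, so the true difference is zero.
- Leavers respond at 20% in both arms: (0.60 − 0.04)/0.80 = 0.70 in each, so the false difference is 0.
- Heat-stone leavers respond at 40%, control leavers at 60%: 0.65 against 0.60, a false difference of 5 points.
- Heat-stone leavers respond at 20%, control leavers at 60%: 0.70 against 0.60, a false difference of 10 points.

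**5. Bias and precision by simulation.** The document supplies baseline NRS 4–6, 60 per arm and about 20% dropout. The assumptions are true response about 64% against 54%, day-7/day-14 correlation 0.7, and dropout after day 7 depending on day-7 response. There were 3000 trials per scenario. A second set of runs used slightly different dropout parameters. Differences are in percentage points; *true* is the nominal or full-data value.

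| Scenario | True | Completers | Imputed from baseline and day 7 |
|---|---|---|---|
| Reasons differ by arm, about 20% each | 10 | 5.7 | 9.5 |
| Same, second set | 9.9 | 4.5 | 9.5 |
| Same dropout rule in both arms | 10 | 9.7 | – |
| Same, second set | 9.6 | 9.2 | 9.5 |

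The completers' shortfall is 10 − 5.7 = 4.3 and 9.9 − 4.5 = 5.4 when reasons differ, and 0.3 to 0.4 when they do not. A further set gave 4.8 against 9.7 (shortfall 4.9) and 9.5 against 9.8 (0.3). If dropout is also unequal (10% against 32%), completers give 3.3 against 10.

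Under the same dropout rule, the SD of the estimate was 9.8 for completers and 9.1 with imputation in the first set: 1 − (9.1/9.8)² = 14% lower variance. Across runs the gain was about 8 to 14%.

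**6. A limit of imputation.** When half of the leavers go before day 7, imputation recovered 7.9 of a true 10.1 points.

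**7. Why baseline NRS matters.** Entry requires NRS 4 to 6. Taking response as a reduction on whole-number scores, 20% is 0.8, 1.0 and 1.2 points from baselines 4, 5 and 6. A patient starting at 4 or 5 needs a 1-point drop; one starting at 6 needs 2. Response is therefore tied to baseline by construction, and the unadjusted test leaves this out.

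**The case against.** The strongest reply is that the article is silent, not wrong. A missing-data rule for one secondary outcome is commonly left to the full protocol or SAP, neither of which is shown. That stands: asking only for such a rule would not be a finding. What the article does fix is the test, and that choice can be judged on its own.

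A reader might go further and infer four things that the documents do not support.
- *That the z test can only delete patients.* It runs on any yes/no variable, including one with missing scored as non-response or imputed. The article does not say that anyone is deleted.
- *That 24 patients will be lost.* The 20% is an allowance. Patients outside the per-protocol set because of treatment failure or an adverse event may still give a day-14 score.
- *That the article contradicts itself on intention-to-treat.* The all-randomized wording in Statistical analysis is attached to the primary analysis. Only the abstract is general, and it names a dataset, not a method for missing scores.
- *That the completers' result is biased.* That depends wholly on assumed dropout patterns, and the bias is near zero when the same dropout rule applies in both arms.

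It is also fair to say that the simulation favours imputation, because dropout depends on the day-7 score that the imputation uses. Step 6 shows the gain shrinking when that fails. Nor is non-responder scoring a safe default. With unequal dropout it gave 16.4 against a true 10, an error of 6.4 points, when completers erred by 6.7.

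**Conclusion.** The point holds as a modest improvement to one secondary outcome. The named test, used on observed scores, fits poorly with the abstract's intention-to-treat statement and leaves out baseline NRS, day-7 NRS and centre.

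The possible bias is roughly 4 to 5 points on a true difference of about 10 when some 20% leave each arm for different reasons. It is larger if dropout rates also differ, and close to zero if the same dropout rule applies in both arms. The variance gain from imputation is about 8 to 14%. All these sizes rest on assumed response rates, correlation and dropout patterns. The case for adjusting for baseline NRS and centre does not depend on any dropout assumption. The primary outcome and the sample size are untouched.

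**What to change.** For the week-2 NRS responder outcome, replace the z test with logistic regression on arm, centre and baseline NRS, reported as a standardized risk difference with a 95% confidence interval. Multiply impute missing week-2 NRS within arm from baseline NRS, day-7 NRS and centre, and derive responder status from the imputed score, so that all randomized patients are included. Add one sensitivity analysis scoring missing as non-response, and report the number missing by arm.

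The cost is a changed clause in the analysis section and a little more programming, with no new data, visits or patients. The drawbacks are that imputation assumes data are missing at random given the scores used, helps little for patients lost before day 7, and is slightly more complex than a z test.
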